| 1. **Sample size considerations**   The main effects of interest in this study are the protective effect of antibiotic treatment (ORAB) and how this effect differs by co-morbidity (ORCO; i.e. the interaction between antibiotic treatment and co-morbidity).  Below, we derive sample sizes needed to detect these effects at 5% significance and 80% power (see Appendix Sample Size Calculation for detailed information on calculations and assumptions). We do so first for COPD patients with a respiratory infection based on previously published effect sizes. We will then relate these sample sizes to patients with other co-morbidities and with urinary or skin/soft tissue infections.  **Respiratory infections**  The power to detect any protective effects depends heavily on the risk of developing the outcome in question.  Past studies looked at a range of individual outcomes, including some extremely rare outcomes with risks as low as 0.04% (e.g. mastoiditis after URTI). They found average effect of antibiotics of ORAB = 0.69.11 and a sample size of ***971,057*** is required to detect this effect in our study.12 To be able to further investigate interactions, i.e. is the protective effect of antibiotics against rare outcomes such as mastoiditis different in patients with COPD versus no COPD, a sample size of **approx. 14 million** patients would be required.13 This is beyond the scope of this study.  Within this study, we will not consider effect sizes in rare outcomes such as mastoiditis individually. Instead, we will look at composite outcomes relevant to patients who consulted for infections, i.e. outcomes such as re-consultations, hospitalisations, etc. (see M. Exposures, Health Outcomes§ and Covariates for details). The risk for these outcomes is much more likely to be around 2.4% previously found for pneumonia.11 For this risk, required sample sizes for the protective effect of antibiotic treatment (ORAB) and how this effect differs by co-morbidity (ORCO) reduce to ***16,512***and ***258,247***.  Assuming a total sample size of at least 3,355,353 found previously (based on only 162 practices11), this study will be powered to detect ORAB and ORCO as small as 0.975 and 0.83, i.e. we will have the power to detect a protective effect of antibiotics against adverse outcomes as small as 2.5% and an increase in effects of antibiotics by 17% points in co-morbid patients.  **Urinary tract and skin/ soft tissue infections**  There are roughly 1/5 as many cases of urinary tract infection and 2/5 as many cases of skin/soft tissue infections as compared to respiratory infections.14 This translates into 671,070 cases of urinary and 1,342,141 cases of skin/ soft tissue infection. No published figures on effect sizes in urinary or skin infections could be found. Assuming similar effect sizes as in respiratory infections, the numbers for both kinds of infection well exceed the minimum sample size of 258,247 needed.  **Other comorbidities**  The powers to detect the same effects for diabetes, CKD, asthma, smoking and obesity are expected to be the same or higher, given the higher prevalence for these conditions (H. Feasibility counts). |

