| 1. **Exposures, Health Outcomes§ and Covariates**   **§***Please note:**Summary information on health outcomes (as included on the ISAC application form above) will be published on CPRD’s website as part of its transparency policy*  *Exposure*  Exposures will include i) prescription of an antibiotic ii) GP consultation for suspected infection (see Appendices: Table 1 – Codelist for antibiotics, Table 2 – Codelist categorising indications for antibiotic use and Table 3 – Codelists to identify patients with suspected respiratory tract, urinary tract or skin/soft tissue infection)  *Health Outcomes*  The following outcomes (within 28 days of presentation in primary care) will be separately considered for analysis:   - Re-consultation for the same type of infection (CPRD; see Appendix Table 3) - Re-consultation for a side effect of antibiotic treatment (CPRD; see Appendix Table 4a –side effects of antibiotic treatment) - Complications of infection in primary or secondary care (CPRD and inpatient HES; see Appendices: Table 4b and 4c – complications of infection; depending on the indication) - Admission to Accident & Emergency (HES A&E) - All-cause hospitalisation (inpatient HES) - All-cause mortality (CPRD, HES and ONS)   We will undertake a sensitivity analysis to investigate the impact of excluding outcomes that occur on the same day as the exposure. The impact of different time windows will be explored, informed by a literature review on the natural history of the duration of different infections.  *Covariates*  We will include the following covariates:   - Age (classified as 0-4, 5-17, 18-44, 45-64, 65-84, 85-94 and 95+, years of age inclusive) - Sex (female and male) - Index of Multiple Deprivation (IMD; 1-5) - Co-morbidities (coded as indicator variables based on national guidance from Public Health England3 and feasibility1; see Appendix Table 5 for comorbidity code list)   - Diabetes   - Chronic Kidney Disease (CKD)   - Chronic Obstructive Pulmonary Disease (COPD)   - Asthma - Obesity - Smoking status15 - Season (months or quarters) and year - Ethnicity   We will undertake a sensitivity analysis of the impact of coding co-morbidities as binary indicator variable and as total number of co-morbidities. |

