| 1. **Data/ Statistical Analysis**   *1. Estimate the incidence of i) GP consultations for infection and ii) antibiotic prescriptions*  For every patient in cohort 1, data on all consultations for infection and antibiotic prescriptions occurring within the study period will be extracted. We will estimate the incidence of GP consultations for infection and antibiotic prescriptions. This will be done for all consultations and prescriptions, and then separately for each category of infection and each class of antibiotics, based on chapter 5.1 of the British National Formulary (BNF) (see Appendix Tables 1 & 2). The denominator will be estimated as total person-time contributed by patients in the cohort during the study period. We will use Poisson regression to estimate the adjusted rate of consultation and prescription, taking account of the effect of age, gender, SES, ethnicity, selected co-morbidity, smoking and obesity. Random effects will be included to take account of clustering of observations by practice. Rates will be assessed for overdispersion by additionally fitting a negative binomial model and testing for alpha greater than zero via a likelihood-ratio test. If rates are found to be overdispersed, the negative binomial model will be used instead of a Poisson model. Adjusted rate ratios will be presented with 95%-confidence intervals.  *2. Describe antibiotic prescribing patterns linked to the reason for prescription*  The overall number of antibiotic prescribing episodes will be calculated for each patient individually, counting all recorded prescriptions between 1st April 2007 and 31st December 2015. For each episode, a clinical indication will be ascertained. Read codes for a diagnosis or symptom of infection recorded on the same day as the antibiotic prescription will be assumed to represent an indication for the prescription. Where more than one possible indication within the same type of infection is recorded on the day of prescription, the more granular code will be used. If multiple indications across different types of infection are recorded, the prescription will be labelled as having multiple indications. Conversely, if no infectious indication for a prescription was found, the prescription will be labelled as having no infectious indication and we will look for any non-infectious codes associated with the date of antibiotic prescription. The ten most common indications will be established and compared to the same numbers for the period from 1998-2001.14 This approach will be replicated for each class of antibiotics based on chapter 5.1 of the BNF. Patterns of repeat consultation or prescription during episodes of infection which may be prolonged will be investigated for each antibiotic prescription extracted in objective 1. We will define a new episode as a consultation or prescription recorded at least 28 days after any previous consultation for infection or antibiotic prescription. We will undertake sensitivity analyses to investigate the impact of using different time periods to define an episode. We will also examine the use of regular (prophylactic) antibiotic treatment.  Proportions and appropriate 95%-confidence intervals will be calculated and all results will be stratified by age-group, gender, SES, ethnicity, selected co-morbidity, obesity and smoking status. Descriptive data will be displayed graphically.  *3. Estimate the incidence of adverse outcomes in the following 28 days*  For each of the selected clinical infection syndromes in the nested cohort study, events in CPRD, HES and ONS will be searched for all adverse outcomes of interest (see *M.* Exposures, Health Outcomes§ and Covariates). Crude incidence rates of for each outcome will be calculated for patients who were treated (exposed) and not treated (unexposed) with an antibiotic. The denominator will be estimated as the total person-time contributed by patients at risk of each adverse outcome, taking account of the fact that this will be different for each outcome. For example, exposed and unexposed patients cannot consult General Practice if they have been admitted to hospital and should therefore not contribute to the denominator during this period when estimating rates of GP re-consultation in the 28 days following consultation for infection. A Poisson regression model will be used to estimate adjusted rates of adverse outcomes in each group, controlling for age, gender, socio-economic status, ethnicity, co-morbidity, obesity and smoking status and assessing for interaction between age and co-morbidity. Random effects will be included to take account of clustering of observations by practice. If the outcomes are overdispersed, negative binomial models will be used instead of Poisson models. Adjusted rate ratios will be presented with 95%-confidence intervals.  *4. Estimate the number of patients needed to treat with antibiotics to avoid one infection-related adverse outcome*  For each clinical infection syndrome-related adverse outcome identified in objective 3, the odds of that outcome in the 28 days following consultation for those treated with antibiotics (unexposed) and not treated with antibiotics (exposed) will be estimated using logistic regression. We will calculate adjusted odds ratios for the protective effect of antibiotics, adjusting for age, gender, SES, ethnicity, year/season, co-morbidity and the probability of receiving antibiotic treatment (see *O. Plan for addressing confounding*) and assessing for interactions with age and co-morbidity. We will use mixed models to adjust for clustering at a practice level and to take account of clustering of observations within a patient due to repeat episodes of infection. Where there is a significant effect of antibiotics between treated and untreated patients, the NNT or NNH to prevent one individual from developing an adverse outcome is calculated as *1/(absolute risk difference)*. A significant effect will be defined by a p-value < 0.05 for the coefficients of antibiotic treatment and its interactions. To avoid an arbitrary cut-off point, p-values close to 0.05 will also be assessed but discussed separately. The NNT will then be used to assess the clinical relevance of any significant differences found. Whilst the relative risk reduction (RRR) may be similar, the NNT may be different due to differing background risk. This will be explored.  *5. Develop risk prediction tools to support clinical decision making*  For each cohort (i.e. for each of the clinical syndromes of UTI, RTI and SSTI), we will develop a logistic regression risk model to predict the risk of adverse outcomes if patients are treated versus not treated with antibiotics. Models will be developed on a random sample of 80% of the observations within a cohort, reserving 20% of the data to estimate the model’s predictive performance.  A negative outcome will be defined as the occurrence of any of the following within 28 days following the index consultation: hospital admission for infection or complication; re-consultation for infection; A&E admission; death. Antibiotic treatment will be defined as a prescription of an antibiotic on the day of consultation for clinical syndrome. Risk factors will be selected based on the analyses outlined in objectives 1-4 and broadly grouped into: socio-demographic variables, co-morbidity and clinical presentation. Biologically plausible interactions between risk factors and age and between risk factors and co-morbidities will be examined.  Whereas age and sex will be forced into the model, other risk factors will be added in order of their significance in objective 4. Risk factors will be kept in the model if they improve the predictive performance of the model as defined by model discrimination and model calibration.17 For example, a risk factor will be used in the model if it improves discrimination and/or calibration. If a variable improves discrimination but reduces calibration, it will still be included in the model, but will be omitted if it increases calibration at the cost of discrimination.  Model discrimination, i.e. the model’s ability to correctly identify patients with and without an outcome, will be estimated using the concordance (c) statistic.18 The c statistic represents the probability that between two randomly chosen patients, one with the outcome and one without, the model assigns a higher score to the patient with the outcome. As a second measure, model calibration will be assessed using the Hosmer-Lemeshow test.18 We will additionally assess model calibration graphically for reasons for poor calibration by comparing the mean observed outcome in deciles of predicted risk. In this calibration plot, the intercept indicates the extent to which predictions are systematically too low or too high, while the slope reflects overfitting of the model.  For each model, we will estimate the internal validity of discrimination and calibration estimates using cross-validation with bootstrap subsampling based on 1000 iterations. In a secondary analysis, we will assess model performance in subgroups by age, sex and co-morbidity.  Finally, we will develop a simplified scoring system using the risk factors in the model,17 assigning the total score to a specific absolute risk of adverse outcomes in the 28 days following consultation, comparing outcomes if an individual is treated versus not treated with antibiotics. We will assess the predictive performance of the risk scores using the approaches outlined above. |

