| 1. **Limitations of the study design, data sources, and analytic methods**   The aim of this study is to make inferences about the effect of antibiotic treatment overall, and in different patient groups in order to develop models to support antibiotic prescribing decisions in primary care. The major challenge is to adjust for confounding by disease severity, i.e. the fact that patients with more severe infections are more likely to be prescribed an antibiotic. Estimating disease severity in primary care is challenging because clinical measures such as vital signs are not well recorded. We have outlined methods to try and account for this issue including the use of instrumental variables and treatment propensity scores.  This study will be limited to some extent in the outcomes it will be able to investigate. First, as shown in I. Sample size considerations, the power needed to identify differences in treatment effects by co-comorbidities will be limited by sample sizes available for extremely rare outcomes. However, as we have chosen our outcomes based on their importance for patients requesting antibiotics, we will look at more common outcomes like re-consultation for which sample sizes should be sufficient. The final effect sizes that we will be powered to detect will then depend on the actual number of observations for respiratory, urinary and skin/soft tissue infections. We will take this a priori power into account when discussing our findings. Secondly, we will rely on the representativeness of the data sources from which we obtain our outcome measures. In particular, HES A&E data coverage is incomplete in comparison to national A&E attendances. We expect this to bias our results for A&E consultations towards the null, limiting our power to detect true differences in outcomes. Again, this limitation will be taken into consideration when discussing any findings on A&E admissions.  By relying on clinical codes to define exposure and measure outcomes, this study may be subject to misclassification. It is known that considerable inter-practice variation exists in coding certain conditions. GPs may not use diagnostic codes to define every episode of e.g. URTI. We will aim to mitigate misclassification of URTIs and other infections by building on comprehensive code lists from previously published studies using CPRD and THIN and reviewing them with experts in the field (see Appendix Table 2). Even so, code lists may not always accurately represent the real reasons why antibiotics were prescribed, as much of the clinical information that is obtained during the consultation is not captured in them. However, one of the main aims of this study is to get a better understanding of this problem through linkage of prescribing and indication. This is further aided by exploring differences in coding between practices will be explored with novel methods, as described in *O. Plan for addressing confounding*.  Although the prescription data recorded in CPRD is of high quality, prescription records themselves do not guarantee that individuals will necessarily take the antibiotics. CPRD data describes antibiotics prescribed and it’s known that patients do not fill 100% of their prescriptions. With no valid way to estimate the proportion of prescribed CPRD antibiotics that were dispensed, we will be unable to ascertain which patients were adherent to the prescribed medications. Furthermore, the antibiotic prescription data used in this work is based on those prescribed from primary care, and thus does not take into account antibiotics prescribed from alternative healthcare sources, such as online, walk-in centres, and urgent care. |

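### The objective 5 tool counts a GP re-consultation the same as admission or death, so its single treated-versus-untreated risk can mask or reverse the contrast for serious outcomes

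*Protocol*

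**What the plan says.** Section M (Exposures, Health Outcomes and Covariates) lists re-consultation, side effects, complications, A&E, hospitalisation and mortality as outcomes that "will be separately considered for analysis". Section N, steps 3 and 4, follows this: each outcome has its own rate and its own odds ratio, with an NNT or NNH where the effect is significant.

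Step 5 departs from it. "A negative outcome will be defined as the occurrence of any of the following within 28 days following the index consultation", and the list is "hospital admission for infection or complication; re-consultation for infection; A&E admission; death". One logistic model per syndrome is to "predict the risk of adverse outcomes if patients are treated versus not treated with antibiotics". The simplified score is then tied to one absolute risk, "comparing outcomes if an individual is treated versus not treated with antibiotics".

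Step 5 contains no weighting, no hierarchy, no model for serious outcomes alone and no risk by component. Its only secondary analysis is by age, sex and co-morbidity. Predictors enter in the order of their objective 4 significance and stay if they improve discrimination or calibration for the composite.

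The only statement on relative frequency is in the Limitations section: "we will look at more common outcomes like re-consultation for which sample sizes should be sufficient".

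**The concern.** The Study Background asks whether prescribing can be cut safely, and the Objectives say the models should support decisions on the need for an antibiotic. That is mainly a question about serious outcomes. An any-event indicator is dominated by its most frequent component. If that component is re-consultation, which partly reflects the behaviour of patients and GPs, the displayed difference will mostly describe return visits.

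A small antibiotic effect on return visits could then cancel or outweigh an effect on admission or death in the figure the GP sees. The user of the tool would have no component figures from which to notice this.

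**Working it through.** **The plan's own figures.** Section I says "we derive sample sizes needed to detect these effects at 5% significance and 80% power" and, for composite outcomes, "The risk for these outcomes is much more likely to be around 2.4% previously found for pneumonia". It takes an odds ratio of 0.69 for antibiotics. With untreated risk p0, treated risk p1 and treated share q, the Wald formula is

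N = (1.960 + 0.842)² × [1/((1−q)·p0(1−p0)) + 1/(q·p1(1−p1))] / (ln OR)².

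- Treated odds: 0.024/0.976 × 0.69 = 0.01697, so p1 = 1.668%.
- The treated share is not in the protocol text, because the sample size appendix is a separate file. Scanning q, 0.80 fits: N = 7.849 × (213.46 + 76.19)/0.13769 ≈ 16,511, against 16,512 stated.
- The same q returns 971,057 at 0.04% risk, as stated, and a detectable odds ratio of 0.975 at N = 3,355,353, as stated.

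These figures are not in dispute. They do show that the 2.4% and the 0.69 come from complications such as pneumonia and are not estimates for re-consultation.

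**Assumptions for the check.** The protocol gives no re-consultation risk (r), no antibiotic effect on it and no risk of admission or death (s). I take r = 5%, 10%, 20% and s = 0.5%, 1%, 2.4%, both untreated, with an odds ratio of 0.69 for serious outcomes and independent components. A&E is not modelled separately.

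**Formulas.**
- Untreated composite: C0 = 1 − (1−r)(1−s).
- Share of composite events that are re-consultation only: r(1−s)/C0.
- Break-even treated re-consultation risk: r* = 1 − (1−C0)/(1−s1), with s1 the treated serious risk. The break-even odds ratio is r*/(1−r*) divided by r/(1−r).

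**Worked cell, r = 10% and s = 2.4%.**
- C0 = 1 − 0.90 × 0.976 = 12.16%.
- Re-consultation only: 0.10 × 0.976/0.1216 = 80%.
- r* = 1 − 0.8784/0.98332 = 10.67%, a 6.7% relative rise, or an odds ratio of 1.075.

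**All cells: re-consultation-only share, then break-even re-consultation odds ratio.**

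| r | s = 0.5% | s = 1% | s = 2.4% |
|---|---|---|---|
| 5% | 91%; 1.03 | 83%; 1.06 | 67%; 1.15 |
| 10% | 95%; 1.02 | 91%; 1.03 | 80%; 1.075 |
| 20% | 98%; 1.01 | 95%; 1.02 | 89%; 1.04 |

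The share falls to about half (49%) when both risks are 2.4%. The break-even odds ratio is then 1.31.

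**Two directions, at r = 10% and s = 2.4%.**
- Re-consultation odds ratio 1.2: treated r = 11.76%, and the composite is 1 − 0.88235 × 0.98332 = 13.24%. That is 1.1 points higher with treatment (composite odds ratio 1.10), while serious risk falls 0.7 points, from 2.40% to 1.67%.
- Re-consultation odds ratio 0.9: treated r = 9.09%, and the composite is 10.61% (odds ratio 0.86). Both contrasts favour treatment.

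**Events available for a serious-outcome model**, 0.8 × N × s, with the section I numbers (3,355,353 respiratory, 671,070 urinary, 1,342,141 skin):
- s = 0.5%: about 13,400, 2,700 and 5,400.
- s = 2.4%: about 64,400, 12,900 and 25,800.

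**The case against.** **The components are reported elsewhere.** This stands for the study's inference. A reader might infer that harm on admission or death would be hidden from the study. It would not be, because objective 4 analyses each outcome separately. The separation is lost only in the tool.

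**Reversal has no empirical support in the protocol.** Correct. It needs antibiotics to raise re-consultation while lowering serious events, and no estimate is given. Only the possibility can be claimed.

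**The 2.4% is not a risk of admission or death.** Also correct. Section I applies a pneumonia figure to composite outcomes generally. It is used here only as the upper end of an assumed range.

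**The calculation is simplified.** Components are unlikely to be independent, and step 3 itself notes that inpatients cannot consult their GP. A high A&E rate would lower the re-consultation share. Both affect the percentages, but neither restores component information to the tool.

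**Predictor selection is not wholly driven by re-consultation.** It would be tempting to say that it is. The order of entry comes from objective 4, where outcomes are separate. Only retention depends on composite performance.

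**The composite is a declared choice, and objective 5 makes no comparison.** The Limitations section says outcomes were chosen for their importance to patients, and aim 5 includes communication with them. That justifies showing re-consultation, but not showing it only when merged with death. The comparison-group section does say that objective 5 attempts no comparison. Step 5 nevertheless displays a treated-versus-untreated contrast, and section O gives inference on the antibiotic effect as a purpose of objectives 4 and 5.

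**Conclusion.** The point holds for the objective 5 tool. Equal counting and the single displayed risk are explicit in step 5. Under the assumed ranges (re-consultation 5–20%, serious outcomes 0.5–2.4%, independence, A&E not separate), 67–98% of composite events are re-consultation only. With an odds ratio of 0.69 for serious outcomes, a re-consultation odds ratio above about 1.01–1.15 turns the displayed contrast against treatment while serious risk falls.

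Two stronger readings are not supported. The documents do not show that the tool will mislead: the direction depends on an unknown re-consultation effect, and at an odds ratio of 0.9 nothing reverses. Nor do they show that the composite must be abandoned. It is a legitimate summary for patients, provided it is not the only figure offered for the decision.

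**What to change.** In step 5, for each syndrome, add a separate model for serious outcomes: admission for infection or complication, or death. Judge retention of predictors on that outcome, and validate the model with the methods already planned. Display its treated and untreated risks. Show re-consultation and A&E risks separately beside any composite, so that the composite is not the sole decision figure.

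No new data or linkage is needed. The costs are more models to build and validate, and lower precision for serious outcomes than for the composite. With the development-sample counts shown above, event numbers look adequate across the assumed 0.5–2.4% range. The actual serious-outcome risk should be tabulated for each syndrome before the models are fitted.

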| 1. **Study population**   The study period will be from 1st April 2007 to 31st December 2015.  We will perform all analyses in patients that were eligible for all linkages and fulfil the following:   1. registered at a participating English practice prior to the transfer of identifiers to the trusted third party for matching for at least a year before their entry into the study 2. their practice is deemed to be contributing ‘up-to-standard' (UTS) data at study start date 3. they had a valid identifier for linkage (NHS number for ONS mortality and HES data, postcode for IMD) 4. they had not opted out or dissented from CPRD or the linkage scheme 5. individual record is of ‘acceptable' research quality as verified by the CPRD.   **Cohort 1**: Individuals who were registered with a GP contributing to CPRD between 1st April 2007 and 31st December 2015 and who have a complete record on age, gender and IMD are eligible for inclusion in this study (see *P. Plans for addressing missing data*). Patients must have been registered with their GP for at least one year before entering the study with the exception of children aged less than one year who will be assumed to be born into the Practice. Patients can enter the study late or leave the study early in order to include patients who died within the study period (who might be inherently less healthy). Patients enter the study population on the latest of the following dates: continuous registration with GP for 12 months or 1st April 2007. Where patients registered with their GP after the 1st April 2007, patients enter the cohort after 12 months of continuous registration. Patients exit the cohort on the earliest of the following dates: the date the patient died, the date the patient left the practice, or 31st December 2015.  Subsequent studies are nested within cohort 1 (see Error: Reference source not found):   1. Nested cross-sectional study: Patients within cohort 1 with at least one prescription of an antibiotic 2. Nested cohort studies of specific infection syndromes: Patients within cohort 1 with at least one GP consultation for a specific infection syndrome (respiratory, urinary, skin/soft tissue). For these cohorts, patients will enter the cohort on the day of the consultation for infection. Patients will leave the cohort on the earlier of: 28 days after initial consultation, death, transfer out of practice or 31st December 2015. Patients can enter and exit the cohort more than once. |

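### The objective 5 treatment definition is not tied to the syndrome, and the multiple-indications label from objective 2 is not carried forward, so one same-day prescription can count as treatment in two syndrome cohorts

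*Protocol*

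**What the plan says.** Section K (Study population) defines each nested cohort as "Patients within cohort 1 with at least one GP consultation for a specific infection syndrome (respiratory, urinary, skin/soft tissue"). On timing it says "For these cohorts, patients will enter the cohort on the day of the consultation for infection", and "Patients can enter and exit the cohort more than once". It does not say whether one day may open an episode in more than one cohort.

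Section N, objective 5, gives the only explicit treatment definition: "Antibiotic treatment will be defined as a prescription of an antibiotic on the day of consultation for clinical syndrome". No drug class or indication is required. Objective 3 speaks only of "patients who were treated (exposed) and not treated (unexposed) with an antibiotic", and objective 4 likewise contrasts treated with untreated patients without giving a day or an indication.

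Objective 2 does foresee the situation. An infection code "recorded on the same day as the antibiotic prescription will be assumed to represent an indication for the prescription", and "If multiple indications across different types of infection are recorded, the prescription will be labelled as having multiple indications". That label is used for describing prescriptions and does not reappear in objectives 3 to 5.

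The outcome definitions also differ. Section M limits re-consultation to the same type of infection. The composite in objective 5 lists re-consultation for infection with no such limit. The covariates in section M and in the Amendments do not include a concurrent infection of another type.

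**The concern.** Read literally, a patient with a respiratory and a urinary code on one day enters both cohorts on that day, and a single prescription makes the patient treated in both. If it was written for the urinary infection, the patient is still a treated respiratory episode. Such patients are plausibly treated more often than patients with one infection, and plausibly at higher risk of admission, A&E attendance or death. They would then gather in the treated arm and make antibiotics look less protective. Under the objective 5 composite, a later urinary re-consultation can also count as an adverse outcome in the respiratory model.

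What is at stake is the meaning of each syndrome's NNT and risk score. If dual infection is commoner in older or co-morbid patients, which the document does not say, the distortion would also differ between the groups the study sets out to compare.

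**Working it through.** **1. The rules side by side.** Objective 2 treats an index day with codes of two infection types as a category of its own. Section K, objective 5 and the covariate lists do not distinguish it. Double entry therefore follows from the absence of an exclusivity rule; the text does not state it outright.

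**2. Inputs.** The Protocol gives neither the frequency of dual coding nor the risk or treatment share on such days. These are assumptions:
- share of index days that are dual, m: 0.5%, 1%, 2%
- risk on dual days relative to single-type days, k: 2 or 3
- share of dual days treated, d: 90%
- share of single-type episodes treated, s: 50% or 80%

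The 80% has indirect support from the Protocol's own sample sizes. With the two-group Wald formula for a log odds ratio (two-sided 5%, 80% power, OR 0.69), n = (1.96 + 0.8416)² × [1/((1−s)·p0(1−p0)) + 1/(s·p1(1−p1))] / (ln 0.69)². Taking p0 = 2.4% (so p1 = 1.668%) and s = 80% gives 16,511 against the stated 16,512. Taking p0 = 0.04% gives 971,057, as stated. With s = 50% the results are 11,817 and 698,278. The sample-size appendix is not at hand, so 80% remains an inference.

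**3. Crude ratio with no true antibiotic effect.**
- Dual share among treated: a = m·d / [m·d + (1−m)·s]
- Dual share among untreated: b = m(1−d) / [m(1−d) + (1−m)(1−s)]
- Risk ratio = [1 + a(k−1)] / [1 + b(k−1)]

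Worked case, m = 1%, k = 3, s = 50%: a = 0.009/0.504 = 1.786%; b = 0.001/0.496 = 0.202%; ratio = 1.0357/1.0040 = 1.032.

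| m | k | s = 50% | s = 80% |
|---|---|---|---|
| 0.5% | 2 | 1.008 | 1.003 |
| 1% | 3 | 1.032 | 1.012 |
| 2% | 3 | 1.062 | 1.024 |

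**4. Benchmark.** Section I claims power for an OR as near to 1 as 0.975, whose reciprocal is 1.026. With s = 50% the middle and upper rows exceed it. With s = 80% no row does; raising d to 95% exceeds it only in the extreme row (1.037).

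**5. A second mechanism, dilution alone.** Suppose dual patients have no extra risk, but in a fraction f of treated episodes the drug did nothing for this syndrome. The treated risk is then (1−f)·p1 + f·p0, with p0 = 2.4% and a true OR of 0.69.

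| f | OR | NNT |
|---|---|---|
| 0 | 0.690 | 137 |
| 1% | 0.693 | 138 |
| 2% | 0.696 | 140 |
| 5% | 0.705 | 144 |
| 10% | 0.721 | 152 |

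Dilution is negligible at 1-2% and becomes material only at about 10% or more.

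**The case against.** The strongest reply is that this is confounding by indication, which section O already describes, including its direction. Section O plans inverse-probability weighting and uses prescribing preference as an instrument, and its severity indicators are offered as examples, so the list is open. Objective 5 also allows risk factors for clinical presentation, which might include co-infection. This stands in part: the crude ratios above overstate what should remain after adjustment. But concurrent infection is not named anywhere as a covariate, objective 5 is described as plain logistic regression with no instrument, and an instrument does not settle which infection a prescription belongs to.

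A second reply is that a handling rule may sit in the appendix code lists or in a statistical analysis plan, neither of which is at hand. That would be enough if the Protocol were merely silent. Here it states the treatment definition itself and distinguishes these days in one objective but not in the next.

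Three stronger readings are tempting and are not supported:
- A reader might infer that dual-coded patients are treated in one cohort by a drug given for the other infection. The records do not show this. Objective 2 takes every same-day infection code as an indication, and one drug may act on both infections.
- A reader might infer that counting one death or admission in two cohorts is itself a bias. The cohorts are analysed separately, so it is not.
- A reader might infer that the bias cancels the smallest effect the study can detect. That depends on assuming 50% of single-type episodes are treated.

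The explicit same-day definition also belongs to objective 5 only; extending it to the NNT in objective 4 is an inference. Section L says objective 5 makes no comparison, yet section O gives objectives 4 and 5 the purpose of inference about treatment.

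**Conclusion.** The point holds as a minor weakness of definition. The stated rule lets one prescription count as treatment in two syndrome cohorts, the existing label is not used where it would help, and objective 5's re-consultation outcome is wider than section M's. The likely direction is against antibiotics. Over the assumed ranges the crude risk ratio is 1.01-1.06 with 50% of single-type episodes treated and 1.00-1.02 with 80%, with less expected after weighting and adjustment. The true size cannot be known until the frequency of multiple-type index days is reported. Nothing here shows that the main conclusions would be overturned.

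**What to change.** In section K and steps 3 to 5 of section N:

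1. Flag every index day, treated or untreated, with codes for more than one infection type. Objective 2 creates this label for prescriptions only, so it must be extended to untreated days.
2. Report how often the flag occurs, by cohort, treatment and age/co-morbidity group.
3. Include the flag in the propensity score and in the outcome models.
4. Give the NNT and risk-model results for single-type index days, with multiple-type days as a separate stratum.
5. Limit the re-consultation component of objective 5 to the same infection type, to match section M.

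The cost is one derived variable and one further set of results. The single-type analysis loses a small share of consultations and applies only to single-syndrome consultations. For that reason it is better shown beside a flag-adjusted analysis of all index days than made the only main analysis, since the tool is meant for ordinary consultations.
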